# Cerebral regional tissue Oxygen Saturation to Guide Oxygen Delivery in preterm neonates during immediate transition after birth (COSGOD III): an investigator-initiated, randomized, multi-center, multi-national, clinical trial on additional cerebral tissue oxygen saturation monitoring combined with defined treatment guidelines versus standard monitoring and treatment as usual in premature infants during immediate transition: study protocol for a randomized controlled trial

**DOI:** 10.1186/s13063-019-3258-y

**Published:** 2019-03-20

**Keywords:** Neonate, Cerebral oxygenation, Immediate transition, Cerebral injury, Mortality

## Abstract

**Background:**

Transition immediately after birth is a complex physiological process. The neonate has to establish sufficient ventilation to ensure significant changes from intra-uterine to extra-uterine circulation. If hypoxia or bradycardia or both occur, as commonly happens during immediate transition in preterm neonates, cerebral hypoxia–ischemia may cause perinatal brain injury.

The primary objective of the COSGOD phase III trial is to investigate whether it is possible to increase survival without cerebral injury in preterm neonates of less than 32 weeks of gestation by targeting cerebral tissue oxygen saturation (crSO_2_) using specified clinical treatment guidelines during the immediate transition period after birth (the first 15 min) in addition to the routine monitoring of arterial oxygen saturation (SpO_2_) and heart rate (HR).

**Methods/Design:**

COSGOD III is an investigator-initiated, randomized, multi-center, multi-national, phase III clinical trial. Inclusion criteria are neonates of less than 32 weeks of gestation, decision to provide full life support, and parental informed consent. Exclusion criteria are severe congenital malformations of brain, heart, lung, or prenatal cerebral injury or a combination of these.

The premature infants will be randomly assigned to study or control groups. Both groups will have a near-infrared spectroscopy (NIRS) device (left frontal), pulse oximeter (right palm/wrist), and electrocardiogram placed immediately after birth. In the study group, the crSO_2_, SpO_2_, and HR readings are visible, and the infant will receive treatment in accordance with defined treatment guidelines. In the control group, only SpO_2_ and HR will be visible, and the infant will receive routine treatment. The intervention period will last for the first 15 min after birth during the immediate transition period and resuscitation. Thereafter, each neonate will be followed up for primary outcome to term date or discharge. The primary outcome is mortality or cerebral injury (or both) defined as any intra-ventricular bleeding or cystic periventricular leukomalacia (or both). Secondary outcomes are neonatal morbidities.

**Discussion:**

crSO_2_ monitoring during immediate transition has been proven to be feasible and improve cerebral oxygenation during immediate transition. The additional monitoring of crSO_2_ with dedicated interventions may improve outcome of preterm neonates as evidenced by increased survival without cerebral injury.

**Trial registration:**

ClinicalTrials.gov Identifier: NCT03166722. Registered March 5, 2017.

## Background

The transition from the intra-uterine to extra-uterine environment is a complex physiological process characterized by major physiological changes in respiratory and hemodynamic functions, which are predominantly initiated by breathing at birth and clamping of the umbilical cord [1]. If hypoxia or bradycardia or both occur, as commonly happens during immediate transition in preterm neonates, cerebral hypoxia–ischemia may cause perinatal brain injury [2–4]. Therefore, protecting the brain from injury is of major importance since up to 10% of infants who survive very preterm birth will develop motor deficits such as cerebral palsy [3] and cognitive deficits [5].

### Monitoring during immediate transition after birth

Routine non-invasive monitoring during immediate transition after birth might include arterial oxygen saturation (SpO_2_) and heart rate (HR) measurement with pulse oximetry/electrocardiogram (ECG), blood pressure, and temperature measurements. Special interest has grown in the use of pulse oximetry and ECG to monitor SpO_2_ and HR during this transitional period [6–10].

However, there is an ongoing debate about the use of supplemental oxygen during neonatal resuscitation. It is still unknown which oxygen concentration is appropriate for preterm infants during immediate transition after birth [10]. In addition, non-invasive monitoring of SpO_2_ does not provide information about adequate oxygen supply to the brain.

Recently, there has been increasing interest in continuous monitoring of cerebral tissue oxygen saturation (crSO_2_) using near-infrared spectroscopy (NIRS) during immediate fetal-to-neonatal transition [2, 11]. In 1992, Peebles et al. reported the first study of NIRS during immediate transition in term neonates and showed a rapid increase of oxygenated hemoglobin and decrease of deoxygenated hemoglobin with initiation of respiration [12]. Further studies showed that crSO_2_ is less affected by mode of delivery (e.g., vaginal delivery versus cesarean section) [13–15] than SpO_2_ and HR. Lower SpO_2_ and HR values have been reported in infants born via cesarean section compared with infants born vaginally [14]. The different behavior of crSO_2_ and SpO_2_ might be due to changes/decreases in cerebral blood flow (CBF) [16]. Differences in arterial oxygen content of the blood or shunting through the patent ductus arteriosus (or both) are most likely the reason for CBF changes/differences [16, 17]. In addition, there is increasing evidence that cerebral tissue oxygenation can be modified by resuscitation interventions in preterm infants [18–21]. It has been demonstrated that preterm infants who need respiratory support showed significantly lower crSO_2_ values compared with those who do not [19].

Therefore, as the brain is the most vulnerable organ of the infant, to monitor cerebral oxygenation in a non-invasive way is a potentially useful to guide supplemental oxygen and respiratory support in neonates. In a two-center prospective observational case control study, we demonstrated that neonates developing an intra-ventricular hemorrhage (IVH) during the first week after birth showed lower crSO_2_ values already during immediate transition compared with neonates without IVH [22].

### COSGOD phase I/II trial

Based on the findings in the observational studies [18–22], preterm neonates of less than 34 weeks of gestation were enrolled in a prospective randomized controlled pilot feasibility study at two tertiary-level neonatal intensive care units (Graz, Austria and Edmonton, Canada) [23]. In an NIRS-visible group, crSO_2_ monitoring in addition to routine monitoring with pulse oximetry and ECG was used to guide respiratory and supplemental oxygen support during the first 15 min after birth. In the NIRS-not-visible group, routine monitoring which consisted of pulse oximetry and ECG was used. The primary outcomes were burden of cerebral hypoxia (<10th centile) or hyperoxia (>90th centile) measured in percentage minutes crSO_2_ during the first 15 min after birth. In the NIRS-visible group, the burden of cerebral hypoxia was halved with a relative reduction of 55.4% (95% confidence interval 37.6–73.2%; *P* = 0.028) [22].

### Assessment of brain injury

Cerebral ultrasonography is a valuable screening tool to determine significant brain injury like IVH grade 1–3 (+ periventricular hemorrhage), cerebellar hemorrhage, and periventricular leukomalacia (PVL) grade 1–3 when conducted regularly over the first weeks of life in preterm infants [24]. Magnetic resonance imaging (MRI) scans of the brain offer even more precise information [25, 26]. However, ultrasound abnormalities in low-gestational-age neonates are already strongly associated with impaired psychomotor and mental development. Children without cranial ultrasound abnormality had the lowest probability of delayed psychomotor or mental development [27].

### Trial objectives

Based on the findings in the observational studies and COSGOD phase I/II trial, the objective of the present clinical trial is to monitor crSO_2_ using NIRS INVOS 5100 (Medtronic, Minneapolis, MN, USA) in addition to routine monitoring of SpO_2_ and HR to guide supplemental oxygen delivery and respiratory/circulatory support in preterm neonates during the first 15 min after birth.

The primary aim is to increase survival without cerebral injury at discharge or term age. The secondary aim is to assess neonatal morbidity until discharge or term age.

We hypothesize that supplemental oxygen support and respiratory/circulatory support guided by crSO_2_ and SpO_2_/HR monitoring during the first 15 min after birth will increase survival without cerebral injury and reduce morbidities in preterm neonates of less than 32 weeks of gestation.

## Methods

### Design

The present trial is an investigator-initiated, randomized, multi-center, multi-national, clinical trial that will enroll 362 preterm neonates of less than 32 weeks of gestation in the study group and 362 preterm neonates of less than 32 weeks of gestation in the control group (Figs. 1 and 2). The trial is carried out in accordance with the Declaration of Helsinki in its latest form and the “International Conference of Harmonization – Good Clinical Practice” (ICH GCP) guidelines.

**Fig. 1 Fig1:**
[figure not shown]
Trial flow chart. Abbreviations: *ECG* electrocardiogram, *ITT* intention-to-treat, *NIRS* near-infrared spectroscopy

**Fig. 2 Fig2:**
[figure not shown]
Schedule of enrolment, intervention and assessments. Abbreviations: *MRI* magnetic resonance imaging, *NIRS* near-infrared spectroscopy

### Patients

Preterm neonates of less than 32 weeks of gestation are eligible for the study. Further inclusion criteria are the decision to provide full life support, written informed consent, and the application of NIRS sensors within 3 min after birth. Exclusion criteria are decision not to provide full life support, no written informed consent, or severe congenital malformation of brain, heart, lung, or prenatal cerebral injury or a combination of these.

### Sample size and statistical analyses

According to data of two European centers (Medical University of Graz and Erasmus Medical Center in Rotterdam) and one Canadian center (Royal Alexandra Hospital in Edmonton), the percentage of neonates who survive without cerebral injury ranges from 56% to 77% and the overall percentage is 65%. Given an increase of neonates who survive without cerebral injury from 65% to 75%, 329 neonates in each group are required to detect this difference with a two-group chi-squared test with a 0.05 two-sided significance level and a power of 80%. Given a dropout rate of 10%, a total of 724 neonates will be enrolled.

Demographic and baseline data for the infants will be compared between groups (study group versus control group) using the chi-squared test or Fisher’s exact test in the case of categorical variables and using the *t* test or Mann–Whitney *U* test in the case of continuous variables. To investigate the primary hypothesis whether the frequency of cerebral injury in preterm neonates of less than 32 weeks of gestation will be different in the two groups, a chi-squared test will be performed. Secondary outcome parameters including mortality and neonatal morbidities (cerebral injury, culture-proven early-onset infection/sepsis, necrotizing enterocolitis, bronchopulmonary dysplasia, retinopathy of prematurity, and persistent ductus arteriosus receiving intervention) will be compared between groups by using the chi-squared test or Fisher’s exact test. Exploratory outcomes (need for respiratory support, intubation, and medications during resuscitation, need for mechanical ventilation and treatment with catecholamines on the first day after birth) will be compared between groups by using the chi-squared test or Fisher’s exact test; trends of monitoring parameters (SpO_2_, HR, and NIRS parameters) during the first 15 min after birth will be analyzed by using linear mixed models. With these linear mixed models, differences in the course of the monitored parameters between groups (study group versus control group) will be analyzed. Baseline characteristics, which will show significant differences between groups, will also be included in the linear mixed models.

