### Outcome measure

The primary outcome measure is survival without cerebral injury defined as any grade of IVH or cystic PVL*.* The secondary outcome measures include mortality and neonatal morbidities (cerebral injury, culture-proven early-onset infection/sepsis, necrotizing enterocolitis, bronchopulmonary dysplasia, retinopathy of prematurity, and persistent ductus arteriosus receiving intervention)*.* The exploratory outcome measures are need for respiratory support, intubation, and medications during resuscitation; need for mechanical ventilation and treatment with catecholamines on the first day after birth; and monitoring parameters (SpO_2_, HR, and NIRS parameters) during the first 15 min after birth.

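### The sentence that assigns the primary test names cerebral injury alone, whereas the primary outcome, the aim and the sample size all use survival without cerebral injury

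*Protocol article*

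**What the plan says.** Most of the article defines the primary endpoint as a composite.

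- Outcome measure: "The primary outcome measure is survival without cerebral injury defined as any grade of IVH or cystic PVL".
- Abstract, Methods/Design, the same composite from the failure side: "The primary outcome is mortality or cerebral injury (or both").
- Trial objectives: "The primary aim is to increase survival without cerebral injury at discharge or term age". The abstract's Background and the Discussion state the same aim.
- Sample size and statistical analyses, on the planned effect: "Given an increase of neonates who survive without cerebral injury from 65% to 75"%. The 329 per group follow from this, for a two-sided 5% chi-squared test with 80% power.

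One sentence departs from this. Later in Sample size and statistical analyses, the chi-squared test for the primary analysis is assigned to "the primary hypothesis whether the frequency of cerebral injury in preterm neonates of less than 32 weeks of gestation will be different" between the groups. The next sentence lists mortality and cerebral injury among the secondary outcomes, each to be compared by chi-squared or Fisher's exact test. Outcome measure has the same secondary list: "The secondary outcome measures include mortality and neonatal morbidities (cerebral injury" and further morbidities).

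**The concern.** The sentence that tells the analyst what to test names a different variable from the one the trial was designed on. Read literally, cerebral injury is tested once as primary and again as secondary, and death is not an event in the primary test.

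This matters because death competes with detection of injury. Under Duration of follow-up and Outcome assessment tools, the scan at 2–24 h is optional and the first scan not so marked is at 2–5 days. An infant who dies before an injury has been seen is a failure on the composite but not on injury frequency. An arm with more such deaths could therefore look better on the stated test.

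Two further consequences follow. The 80% power was not calculated for that test. And a confirmatory trial with two readings of its primary test leaves room to choose between them after results are known.

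**Working it through.** **Inputs from the article.** Survival without cerebral injury 65% v 75% (so death or injury 35% v 25%); two-sided α = 0.05; power 80%; chi-squared test; 1:1 allocation; 329 per group before dropout.

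**Step 1: reproduce the plan's figure.** With pooled variance and no continuity correction,

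n = [z₀.₉₇₅·√(2·p̄·q̄) + z₀.₈₀·√(p₁q₁ + p₂q₂)]² / (p₁ − p₂)²

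= [1.960·√(2·0.70·0.30) + 0.842·√(0.65·0.35 + 0.75·0.25)]² / 0.10²

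= (1.2702 + 0.5422)² / 0.01 = 328.5, so 329 per group.

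Power at 329 is 80.1%. The sample size is thus reproduced with the composite rates.

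**Step 2: power of the test as worded.** The article gives no rate for injury alone, so this needs assumptions. Let m be the share of controls who die without detected injury, counted here as uninjured. Control injury is then 35% − m. The composite is held at 35% v 25% throughout, and

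power = Φ{[|p₁ − p₂|·√329 − 1.960·√(2·p̄·q̄)] / √(p₁q₁ + p₂q₂)}.

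Three ways of sharing out the 10-point gain (injury rates, control v study, then power):

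| Assumed m | Both components fall by the ratio 25/35 | All 10 points in injury | Gain comes first from fewer such deaths |
|---|---|---|---|
| 3% | 32.0% v 22.9%: 74.9% | 32% v 22%: 82.5% | 32% v 25%: 51.2% |
| 5% | 30.0% v 21.4%: 71.2% | 30% v 20%: 84.3% | 30% v 25%: 30.0% |
| 8% | 27.0% v 19.3%: 65.1% | 27% v 17%: 87.4% | 27% v 25%: 8.4% |
| 10% | 25.0% v 17.9%: 60.8% | 25% v 15%: 89.6% | 25% v 25%: 2.5% |

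Worked line, m = 3%, common ratio: (0.0914·18.138 − 1.960·0.6310)/0.6276 = 0.672, and Φ(0.672) = 74.9%. The last cell (2.5%) has no difference in injury left to detect; the figure is the chance of a significant result in the favourable direction only.

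**Step 3: can the two tests disagree?** Take a hypothetical case, control v study: injury 30% v 21%, death without detected injury 5% v 14%. The composite is 35% in both arms.

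- Such deaths counted as uninjured: z = 0.09/√(2·0.255·0.745/329) = 2.65, p = 0.008.
- Such deaths treated as missing: 98.7/312.6 = 31.6% v 69.1/282.9 = 24.4%. Pooled p = 0.282, standard error √[0.282·0.718·(1/312.6 + 1/282.9)] = 0.0369, z = 1.94, p = 0.052.

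A composite with no difference can thus sit beside a significant or borderline result on injury alone, depending on a coding rule that the article does not state.

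**The case against.** The best defence is that this is a drafting slip. The composite is stated consistently in the abstract, the objectives, the sample size, the outcome section and the Discussion. Only one sentence departs from it, and because injury is listed separately as secondary, that sentence may be shorthand. This is plausible, but it does not remove the contradiction in the sentence that fixes the primary analysis.

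Four stronger readings are tempting, and the document does not support them.

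- *The composite is never tested.* The sample size sentence ties a two-group chi-squared test to the 65% v 75% difference. The section conflicts with itself; it is not silent on the composite. Nor does the wording prove what will be done.
- *Deaths drop out of the analysis.* The article does not say whether infants who die without detected injury would be excluded or counted as uninjured, and some early deaths will have had the optional scan. What follows from the wording is only that death is not itself a failure.
- *The primary test is underpowered.* Step 2 shows power on either side of 80%, depending on assumptions that the article cannot settle.
- *Excess deaths would be hidden.* Mortality is a secondary outcome and the reportable serious adverse event, and under Safety an independent committee looks at primary and secondary outcomes. An excess would be visible, though outside the primary test.

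The example in Step 3 is also extreme: death without injury nearly triples, with no basis in the document. It shows that the tests can diverge, not that they will.

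**Conclusion.** The point holds as a misstated primary analysis variable. It is not a detail left to an analysis plan, because the article names the test and the variable, and the variable contradicts its own outcome definition, aim and sample size.

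The firm part needs no assumption: the stated test does not count death as a failure, and its power was not the one calculated. The size of the effect on power is not derivable. Over an assumed 3% to 10% of controls dying without detected injury (counted as uninjured), with 329 per group, it runs from 89.6% down to 2.5% across the three scenarios. The divergence example (p = 0.008 or 0.052 with no difference in the composite) is hypothetical and depends on how those deaths are coded.

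**What to change.** In Sample size and statistical analyses, replace the frequency of cerebral injury in the primary test sentence with: *the proportion surviving without cerebral injury (any-grade IVH or cystic PVL), with every death up to the primary time point counted as a failure, whether or not the infant was scanned.* Apply it in the analysis population that the protocol defines. The correction need not set a new one, which matters because infants are randomised before birth while sensor placement within 3 min is an inclusion criterion and consent may be deferred.

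Keep cerebral injury alone and mortality alone as secondary outcomes. Carry the same wording into any statistical analysis plan before outcome data are compared by arm.

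The cost is one sentence. No new data are needed, and 329 per group (724 enrolled) stands, since it was calculated for the composite.

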### Randomization

Neonates will be randomly assigned before birth to either the study group or the control group by using the web-based randomization service (“Randomizer for Clinical Trials”), developed at the Institute for Medical Informatics, Statistics and Documentation, Medical University of Graz (https://www.randomizer.at/random/). The ratio of allocation is 1:1. Patients will be stratified according to trial site. In case of multiple births, only the first infant will be randomly assigned.

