### Monitoring

The antepartum medical history and birth history will be collected. Gestational age, birth weight, gender, pH of umbilical artery, and Apgar score will be documented for each neonate. Continuous positive airway pressure and positive pressure ventilation with a face mask, if necessary, will be performed.

Monitoring during the first 15 min after birth consists of (i) pulse oximetry for SpO_2_ and HR as routine non-invasive monitoring, (ii) ECG for HR as routine non-invasive monitoring, and (iii) NIRS measurements. NIRS measurements will be blinded in the control group.

For NIRS measurements, the Invos™ Cerebral/Somatic Oximeter monitor (Medtronic) with the neonatal sensor will be used.

Immediately after birth, when the neonate is brought to the resuscitation area, the cerebral NIRS sensor will be placed on the left forehead and fixed with a continuous positive airway pressure cap or elastic bandage on the left forehead. ECG electrodes will be applied to the chest for HR monitoring. One pulse-oximetry sensor will be applied to the right palm or wrist for monitoring pre-ductal SpO_2_ and HR.

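### Randomisation is stratified by site and site rates run from 56% to 77%, yet the primary test is a crude chi-squared that ignores both site and gestational age and so gives away some power

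*Protocol article*

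**What the plan says.** The Randomization section of the protocol article allocates 1:1 and names one stratification factor: "Patients will be stratified according to trial site".

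The section on sample size and statistical analyses reports pre-trial data from three centres, in which "the percentage of neonates who survive without cerebral injury ranges from 56% to 77"%, with 65% overall. It sizes the trial for a "two-group chi-squared test with a 0.05 two-sided significance level and a power of 80"% and then fixes the same kind of test for the primary hypothesis: "a chi-squared test will be performed". Neither site nor any baseline variable enters that test.

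The Monitoring section states: "Gestational age, birth weight, gender, pH of umbilical artery, and Apgar score will be documented for each neonate". The only covariate adjustment in the article is in the linear mixed models for the exploratory monitoring trends, where covariates enter if they differ significantly between groups at baseline.

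**The concern.** When allocation is balanced within site and site predicts outcome, the difference between arms varies less from trial to trial than a two-group chi-squared test assumes. The test leaves the between-site variation in its error term, so its standard error is too large. The direction is safe for type I error, but power is lost and the analysis does not follow the design.

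Gestational age is a second, separate loss. It is known for each infant, the intervention cannot change it, and it is not a stratification factor. Eligibility covers everything below 32 weeks. If it predicts survival without cerebral injury, leaving it out costs precision, and an imbalance that happens to arise will not be corrected in the primary estimate.

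The power at stake is small, but the trial is planned at 80% with no margin.

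**Working it through.** **Inputs from the article:** 65% v 75%, two-sided 0.05, 80% power, 329 per group, 1:1 allocation stratified by site, centre rates 56-77% with 65% overall.

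**Assumptions (not in the article):** the number and mix of sites, and the distribution and effect of gestational age.

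**1. The plan's own figure.** With pooled variance and no continuity correction,

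n = [1.96·√(2·0.70·0.30) + 0.842·√(0.65·0.35 + 0.75·0.25)]² / 0.10² = (1.270 + 0.542)² / 0.01 = 328.5, rounded up to 329 per group.

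Power at 329 is 80.1%. The article's figure reproduces for the crude test.

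**2. Why the crude test is conservative.** Take three equal sites at 56%, 62% and 77% (mean 65%).

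- Between-site variance: (0.09² + 0.03² + 0.12²)/3 = 0.0078.
- Variance used by the crude test under the null: 0.65·0.35 = 0.2275.
- Share due to site: 0.0078/0.2275 = 3.4%.
- True standard deviation of the crude z statistic: √(1 − 0.034) = 0.983.
- Effective critical value: 1.96/0.983 = 1.994, which gives a two-sided error of about 4.6%.

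The widest mix that the range allows is 12/21 of infants at 56% and 9/21 at 77%. Its site share is (12/21)(9/21)(0.21²)/0.2275 = 4.7%, and the error is about 4.5%.

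**3. Site only, simulated (329 per group, 200,000 runs).** A common odds ratio was set to raise the overall rate by 10 points.

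| Sites | Type I, crude | Type I, CMH | Power, crude | Power, CMH |
|---|---|---|---|---|
| Three equal, 56/62/77% | 4.6% | 5.0% | 80.6% | 81.4% |
| Two-point mix, 56% and 77% | 4.5% | 5.0% | 80.6% | 81.9% |
| Ten, spread over 56-77% | 4.7% | 5.0% | 80.5% | 81.0% |

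CMH is the Cochran-Mantel-Haenszel test by site. It gains about 0.5-1.2 points.

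**4. Site plus gestational age, simulated (3,000 runs per scenario, 658 infants, three sites).** Each figure has a simulation error of about 0.7 points.

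Mean 29.0 weeks, SD 1.8 assumed:

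| Assumed odds ratio per week | Crude | Logistic with site and gestational age |
|---|---|---|
| 1.0 (no effect) | 79.6% | 80.3% |
| 1.15 | 81.0% | 82.6% |
| 1.3 | 81.9% | 83.5% |
| 1.5 | 79.3% | 83.7% |

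Mean 28.8 weeks, SD 2.2 (clipped at 23-31.9 weeks) assumed:

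| Assumed log-odds slope per week | Crude | CMH | Logistic with site and gestational age |
|---|---|---|---|
| 0.2 | 81.3% | 82.1% | 83.4% |
| 0.3 | 80.9% | 81.7% | 84.7% |
| 0.4 | 80.8% | 81.8% | 86.2% |

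With six sites and slope 0.4 the figures are 80.1%, 80.8% and 85.6%. A slope of 0.4 is an odds ratio of about 1.5 per week, so the last rows of the two tables differ mainly in the assumed spread of gestational age. Type I error stayed near 5% for all the methods.

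**5. Margin.** The enrolled total is 2 × 362 = 724. After 10% loss, 362 × 0.90 ≈ 326 per group remain, with power of 79.7%. The crude analysis therefore has no reserve.

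**The case against.** The planned test is valid, and it is the test for which the sample size was computed, so the trial is not underpowered against its own plan. The error is on the safe side. The part that rests on the article's own figures is worth about one point of power, which is unlikely to change a conclusion. The 56-77% range comes from three centres before the trial, and the spread across the sites of a multi-national trial may be narrower. The larger gain needs a gestational-age effect that the article does not give. Chance imbalance is already covered by the test's error rate. The logistic option also needs a rule for small sites and a standardisation step, and an unseen analysis plan may add an adjusted analysis.

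Much of this stands. There is no bias and no excess of false positives, the site gain is small, and the gestational-age gain is conditional. The imbalance argument is about precision and the estimate in the trial at hand, not about validity.

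It does not remove the point. The article itself names the primary test, so this is not a detail left open for the analysis plan. The stratification factor is not carried into that test, and the direction of the loss is the same in every scenario examined. With no gestational-age effect at all, the adjusted model was no worse than the crude test.

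**Conclusion.** The concern holds, as an improvement that should be made and not as an error of validity. Ignoring site makes the crude test run at about 4.5-4.7% instead of 5% and costs about 0.5-1.2 points of power. This assumes that the trial sites spread as the three pre-trial centres did.

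Leaving out gestational age as well brings the total loss to about 1-4 points for odds ratios of 1.0-1.5 per week with an SD of 1.8 weeks. With an SD of 2.2 weeks and slopes of 0.2-0.4 it is about 2-5.5 points. These last figures depend wholly on the assumed effect and spread. The sample size of 329 per group is correct for the crude test.

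**What to change.** Before unblinding, name one of these as the primary analysis:

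- a Cochran-Mantel-Haenszel test stratified by site, with the common risk difference and its 95% confidence interval; or
- a logistic model with group, site and gestational age, with a pre-specified rule for pooling small sites, reporting the marginal risk difference and its 95% confidence interval so that the result stays on the scale of the 65% v 75% planning difference.

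The first is the minimum that respects the stratified design. The second also captures the gain from gestational age. Keep the crude chi-squared test as a sensitivity analysis, and fix the covariates in advance instead of choosing them by baseline significance.

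The cost is wording in the analysis plan. No new data, visits or infants are needed. The choice should be on record before results are known, because a later switch from the published crude test would be open to challenge.

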### Outcome assessment tools

All-cause mortality will be recorded. Cerebral injury will be assessed by cerebral ultrasound at 2–24 h (optional), 2–5 days, 6–8 days, 12–16 days, before discharge/37–42 weeks and optionally cerebral injury will be assessed by cerebral MRI, if performed routinely—mainly without sedation during postprandial sleep—before discharge or term age (37–42 weeks of gestation). Case history will be assessed until discharge or term age, depending on what comes first.

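### BPD and ROP are compared as stand-alone outcomes although early death precludes them, so if mortality differs the arm with fewer deaths can look worse on both

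*Protocol article*

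**What the plan says.** Under Outcome measure, the protocol article states that "The secondary outcome measures include mortality and neonatal morbidities" and then lists the morbidities, BPD and ROP among them. Sample size and statistical analyses repeats the list ("Secondary outcome parameters including mortality and neonatal morbidities (cerebral injury, culture-proven early-onset infection/sepsis, necrotizing enterocolitis, bronchopulmonary dysplasia" and so on) and assigns each item a two-group test: the list ends "bronchopulmonary dysplasia, retinopathy of prematurity, and persistent ductus arteriosus receiving intervention) will be compared between groups by using the chi-squared test", with Fisher's exact test as the alternative. Mortality and each morbidity are thus separate binary outcomes.

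The primary outcome is built differently: "The primary outcome measure is survival without cerebral injury defined as any grade of IVH or cystic PVL". There an infant who dies is a failure and cannot be counted as uninjured. None of the secondary morbidities has that protection.

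Trial objectives puts forward the hypothesis that the guided support "will increase survival without cerebral injury and reduce morbidities in preterm neonates of less than 32 weeks of gestation". Follow-up is bounded as follows: "Case history will be assessed until discharge or term age, depending on what comes first" (Outcome assessment tools).

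**The concern.** BPD and ROP are diagnosed late in the neonatal course, so an infant who dies in the first days or weeks cannot acquire either diagnosis. The stated test can be run on two denominators, and a mortality difference disturbs both.

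- **All randomised infants.** Each early death enters as an infant without BPD or ROP. The arm with more deaths gains apparent non-events.
- **Survivors only.** The groups compared are selected by an event that follows randomisation. If one arm keeps alive additional infants at higher than average risk, its survivors are a sicker group.

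The distortion runs in both directions: fewer deaths can appear as more BPD, and more deaths as less BPD. What is at stake is the answer to the secondary aim on neonatal morbidity, for these two outcomes. Choosing one denominator rather than the other does not remove the problem. It has to be met by adding an outcome that includes death, or by a rule for reading the morbidity beside mortality.

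**Working it through.** **The plan's own figure.** "Given an increase of neonates who survive without cerebral injury from 65% to 75%, 329 neonates in each group are required", at two-sided 0.05 and 80% power. With a pooled variance under the null hypothesis and mean rate 0.70:

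n = [1.960 × √(2 × 0.70 × 0.30) + 0.842 × √(0.65 × 0.35 + 0.75 × 0.25)]² / 0.10² = 328.5, so 329 per group. The figure reproduces, and 329 per arm is used below.

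**Inputs that the article does not give (assumed).**
- Mortality: d_C = 10% control, d_S = 5% study.
- BPD in infants who would survive in either arm: m = 25%, the same in both arms (no effect on BPD).
- BPD in the extra survivors of the study arm: h = 60%, varied from 40% to 80%.

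**Formulas.**
- All randomised: control (1 − d_C)m; study (1 − d_C)m + (d_C − d_S)h. The shift is (d_C − d_S)h.
- Survivors only: divide by 1 − d_C and 1 − d_S. The shift is (d_C − d_S)(h − m)/(1 − d_S), which is zero if h = m.
- Death or BPD: add d_C and d_S to the all-randomised rates.

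**Results at h = 60%.**
- All randomised: 0.90 × 0.25 = 22.5% v 22.5% + 0.05 × 0.60 = 25.5%; shift +3.0 points.
- Survivors only: 22.5/0.90 = 25.0% v 25.5/0.95 = 26.8%; shift +1.8 points.
- Death or BPD: 10 + 22.5 = 32.5% v 5 + 25.5 = 30.5%; difference −2.0 points.

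**Range over h, and the chance of a significant all-randomised result against the arm with fewer deaths (normal approximation, 329 per arm; nominal 2.5%).**

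| h | All randomised | Survivors only | Death or BPD | Chance |
|---|---|---|---|---|
| 40% | +2.0 | +0.8 | −3.0 | 9% |
| 60% | +3.0 | +1.8 | −2.0 | 14% |
| 80% | +4.0 | +2.9 | −1.0 | 22% |

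**Smaller mortality gap.** With 10% v 8%, the all-randomised shift is 0.02 × h = +0.8 to +1.6 points for h from 40% to 80%, and the chance is 4% to 7%. With 5% v 3% the gap is again 2 points and the shift is the same. It falls to 0.02 × 0.20 = +0.4 points if the extra survivors have only a 20% rate.

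**The case against.** **A statistical analysis plan usually fixes the denominator.** That is so, and an article need not define each morbidity. But the article does fix BPD and ROP as stand-alone outcomes and fixes their test, and neither denominator by itself makes that comparison safe when mortality differs. If an analysis plan already adds an outcome that includes death, the point is met.

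**The hypothesis is not better survival as such.** This stands. A reader might infer that the comparison is biased precisely when the trial's hypothesis is true. The documents do not support that: the hypothesis and the 65% to 75% assumption concern the composite, survival without cerebral injury. The composite can improve entirely through less haemorrhage, with equal mortality, and then the distortion does not arise.

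**Every rate is assumed.** This stands too. Even the +3.0 points is about 0.9 of a standard error (3.3 points with 329 per arm), and the survivors-only shift vanishes if the extra survivors carry average risk.

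**Death or BPD is not a measure of BPD.** A reader might infer that only the composite points the right way. It does not show an effect on BPD: in the example the true effect is zero, and the −2.0 points is the 5-point mortality gain less the 3 points of BPD in the extra survivors. The composite therefore belongs beside the stated outcomes and should not replace them.

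**Mortality is already a separate secondary outcome.** True, and a careful reader would look at both. That limits the harm, but it does not tell the reader how far a BPD difference is a by-product of deaths.

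**Conclusion.** The point holds for BPD and ROP, as a weakness in how two secondary outcomes would be read. If mortality differs, the all-randomised comparison shifts against the arm with fewer deaths. The survivors-only comparison shifts the same way when the extra survivors are at higher than average risk. Under the assumed 10% v 5% mortality the all-randomised shift is +2 to +4 points. With a 2-point mortality gap it is about 1 point (0.8 to 1.6 over the same range of h), and with equal mortality nothing need change. The article supplies none of these rates, so the size cannot be settled from it.

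The point does not reach the primary outcome, which already joins death to cerebral injury. Nor does it require every morbidity to be redefined. Death or cerebral injury would nearly duplicate the primary outcome. Early-onset sepsis is diagnosed early, and necrotising enterocolitis and treated ductus can stay as stated with deaths shown alongside.

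**What to change.** For BPD and for ROP, add a between-group comparison of death before assessment or the morbidity, in all randomised infants, using the test already stated. Show the counts of deaths and of the morbidity beside it in each arm. State that any conclusion about reduced BPD or ROP will rest on these results read together with mortality. Keep the stated secondary outcomes, including mortality on its own.

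The cost is a few lines of wording in the protocol or analysis plan and a few table rows, with no new data and no more infants. The small downside is that the composite partly reflects mortality and is not a pure morbidity effect, which is why the components stand beside it. The wording is best settled before unblinding.
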